## Abstract

**Background:**

There is limited evidence on the efficacy and social utility of cognitive training. To address this, we have designed a randomized controlled trial to assess the effectiveness of memory training workshops for healthy older people in terms of their short- and long-term impact on cognitive function, health-related quality of life, and functionality.

**Methods/design:**

A randomized controlled trial will be performed in health care centers in Barcelona (Spain) through comparison of a group of individuals participating in memory training workshops (experimental group) with another group with similar characteristics not participating in the workshops (control group). The intervention will consist of twelve 90-minute group sessions imparted once a week by a psychologist specialized in memory training. The groups will each comprise approximately 15 people, for a total number of 230 patients involved in the study. Each session has its own objectives, materials and activities. The content of the intervention is based on memory training from different perspectives, including cognitive and emotional aspects and social and individual skills. Data will be collected at baseline, at 3–4 months and at 6 months. To assess the efficacy of the intervention on cognitive function, health-related quality of life and functionality, a statistical analysis will be performed by fitting a repeated-measures mixed effects model for each main outcome: *Self-perceived memory,* measured by a Subjective Self-reported Memory Score (from 0 to 10) and by the Memory Failures in Everyday life questionnaire (MFE); *Everyday memory,* measured using the Rivermead Behavioural Memory Test-3 (RBMT-3) and *Executive control abilities,* measured in terms of visual-perceptual ability, working memory and task-switching ability with the Trail Making Test (TMT) and with the digit span scale of the Wechsler Adult Intelligence Scale III (WAIS III).

**Discussion:**

The results of this study will be highly useful for social and public health policies related to older people. Given the continuous increase in the prevalence of older people, a large number of interventions targeting memory loss are funded by public resources. To ensure transparency and effective prioritization, research such as the present study is needed to provide evidence of the effectiveness and usefulness of these interventions.

**Trial registration:**

Number: NCT02431182.

## Background

Social changes in the twentieth century have been characterized by worldwide population aging, especially in developed countries. This has led to major changes in disease distribution, with an increase in the prevalence of chronic and degenerative diseases, including cognitive impairment and dementia. Between 2000 and 2050, the proportion of the global population older than 60 years will double from approximately 11 % (605 million people) to 22 % (2 billion people) [1]. In Spain, the estimated proportion of people older than 64 years in 2050 is approximately 30 % of the population [2]. In 2012, an estimated 8.4 million people aged 60 years and older had dementia in European Union member states, accounting for 7 % of the population in that group. Spain had one of the highest prevalence rates of dementia, which affects more than 7.5 % of the population aged 60 years and older [3].

Consequently, there is increased interest in new pharmacologic treatments for dementia as well as in non-pharmacological preventive interventions. These non-pharmacological interventions are mainly based on cognitive training to optimize the performance of existing functions and to decrease the risk of cognitive impairment. The benefits of teaching rehabilitative and compensatory strategies in older persons who already have memory complaints have been shown in multiple studies [4]. However, the evidence on the effects of cognitive training on cognition in healthy elderly persons is less conclusive [5]. A systematic review of randomized controlled trials in healthy older persons concluded that training improved immediate performance on related tasks, but that there was no evidence for any generalizability of training [5]. Among the studies included in that review, a notable publication was the ACTIVE trial, which included 2800 healthy elders. In that trial, participants demonstrated significant changes in each of the three cognitive abilities for which they had received training: memory, inductive reasoning, and speed of processing. The authors estimated that the magnitude of the observed effect was equivalent to avoiding the impairment that would take place in the natural course of life of healthy people in a period between 7 and 14 years [6]. Overall, some of the characteristics associated with the success of the interventions described were the group structure, the duration (at least 8–10 sessions) and the intensity (60–90 minutes each session). In terms of content, there was no clear pattern of methods or strategies, although most of the interventions that were successful used memory training techniques, especially for episodic memory [7, 8].

Given the limited evidence available on the efficacy and social utility of cognitive training, we have designed a randomized controlled trial to assess the effectiveness of cognitive training through memory training workshops offered to healthy older persons in terms of their immediate and delayed impact on cognitive function, health-related quality of life and functionality.

The paper partially meets the requirements for the PhD program of [name] at the Pompeu Fabra University (Barcelona, Spain).

### Hypothesis

The group memory training intervention proposed in this protocol will significantly improve cognition (memory, attention and executive control abilities) and health-related quality of life (HRQoL) in the experimental group (EG) compared with the control group (CG).

### Objectives

#### Principal objective

To assess the efficacy of a memory training workshop in improving self-perceived memory, everyday memory, and executive control abilities.

#### Secondary objective

To assess the effect of the memory training workshop on HRQoL and on late-life function and disability.

## Methods

### Study design

This is a randomized controlled trial, comparing a group of individuals taking part in the memory training workshops (EG) with another group with similar characteristics not attending the workshops (CG). Data will be collected at baseline and at 3 and 6 months.

### Study setting and participants

The study will be conducted in health care centers in Barcelona (Spain). Included participants comprise healthy older people registered in any of the four health care centers included in the study and meeting the inclusion criteria. The inclusion criteria are: a) men and women aged between 65 and 80 years (inclusive) who consent to participate in the study; b) not presenting with diagnoses of dementia or cognitive impairment measured through the Mini-Mental State Examination (MMSE >24) [9, 10] and c), absence of depression measured using the Geriatric Depression Scale (GDS 5 ≤ 2) [11]. The exclusion criteria are: a) having participated in a memory training program within the last 3 years; b) having a severe sensorial disability and c) being unable to read or write. Each participant has the right to withdraw from the study at any time. In addition, a participant may be withdrawn from the study if deemed necessary by the researchers based on any of the following withdrawal criteria: a) adverse experience; b) significant non-adherence to the intervention (missing more than 50 % of the sessions); c) loss-to-follow-up; d) clinical conditions not allowing the participant to continue in the study (such as illness and accident); and e) death.

Description of the study (Figure 1):

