### Description of the intervention

Once the baseline assessment has been conducted, individuals in the EG will start the multifactorial intervention. The memory training workshop is designed to stop or delay age-related memory losses and promote personal autonomy, thus enhancing mental and physical wellbeing. Specifically, these workshops aim to broaden knowledge on memory function, improve memory processes, and increase self-esteem and quality of life by providing some strategies (i.e., strategies for collecting and coding information) and relational space. The intervention will consist of twelve 90-minute group sessions provided once a week by a psychologist specialized in memory training. The groups will be composed of around 15 people. Each session will have its own objectives, materials, and activities (Table 2). The content of the intervention is based on memory training from different perspectives such as cognitive and emotional aspects and social and individual skills.

**Table 2 Tab2:** Contents of the memory training workshop by session

SESSION	CONTENT
1	Presentation of the workshop: Objectives and Methodology
2	Types of memory I: Explanation of the different types of memory and their role in normal life
3	Types of memory IIa: Strategies for gathering and codifying information.
4	Types of memory IIb: Strategies for selecting and storing information.
5	Types of memory III: Strategies for gathering, codifying, selecting, storing and retrieving information. Importance of the context and the meaning of things. Semantic and episodic memory.
6	Types of memory IV: Strategies for gathering, codifying, selecting, storing and retrieving information. Individual differences.
7	Types of memory V: Strategies for retrieval according to individual profile. Improving self-esteem.
8	Types of memory VI: Strategies for recovering social skills.
9	Personal and social skills
10	New contexts and opportunities. Conceptual maps (physical and mental).
11	Evaluation of the workshop.

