### Statistical analysis

Baseline comparability between the study arms will be assessed through bivariate analyses of the pre-test data set group (dependent and independent variables) comparing the control and the experimental arms. The chi-square test will be used to compare qualitative data, as well as the Student *t* test or the Mann–Whitney test for quantitative data, depending on the normality of the distribution. If differences are found in baseline characteristics, we will consider adjusting for these variables in the efficacy analysis.

A descriptive analysis will be conducted for results at baseline, at the immediate follow-up and at the delayed follow-up for the EG and CG. Categorical outcomes will be described through raw frequencies or percentages, and continuous outcomes will be described through mean scores and standard deviations. Effect measures for each outcome at the immediate and delayed follow-ups will be computed as the mean of the differences of the aggregated scores for the EG and CG. Effect measures will be presented with their 95 % confidence intervals.

The main statistical analyses to assess the efficacy of the intervention on self-perceived memory, everyday memory and executive control abilities will be performed using a repeated-measures mixed effects model for each main outcome defined in the protocol [34]. In each model, the independent variables will be the group (EG or CG), time (baseline, immediate follow-up or delayed follow-up) and any relevant characteristics that differ between the groups at the baseline assessment (e.g., age or educational level). An interaction term between time and group will be included in the analyses. The models will be fitted with the available data, ignoring missing data.

To determine whether the results have been influenced by missing data, we will conduct sensitivity analyses by fitting the models with completed datasets obtained by imputing the missing data [35]. In this analysis, missing values for the immediate or delayed post-test assessments will be imputed through the Last Observation Carried Forward (LOCF) strategy. According to this strategy, missing values will receive the value obtained by the participant in the previous assessment. In addition, we will perform sensitivity analyses restricted to those participants attending at least 80 % of the sessions.

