### Strengths and limitations

Our study has some important strengths; it is the first randomized controlled trial aiming to demonstrate the effectiveness of memory training in healthy older people in Spain. Additionally, we will apply a wide variety of validated tests, which will allow for assessment of the potential impact of the intervention on several health-related outcomes (memory, other executive control abilities, HRQoL, life function and disability), as well as comparisons with other studies.

A possible limitation is the length of follow up, less than 1 year, which may negatively affect our results because some increases in memory problems may not be detected. Another limitation of our study is that it does not include a matched active control group. Therefore, we will not be able to isolate the memory training effects from the potential confounding benefits of increased social contact.

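### Poor attendance can be a reason to withdraw a participant from the study, which only the workshop arm can trigger, so the rule can create avoidable missing outcomes in one arm of the main analysis

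*Protocol article*

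**What the plan says.** Under Study setting and participants, the article states that "a participant may be withdrawn from the study if deemed necessary by the researchers" on any of five grounds. The second is "significant non-adherence to the intervention", set at missing more than 50% of the sessions. The withdrawal is from the study, not merely from the workshop, and it is discretionary.

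Under Description of the intervention: "The intervention will consist of twelve 90-minute group sessions provided once a week". On twelve sessions the criterion means seven or more missed. Study design defines the control group (CG) as people who do not attend the workshops, and Strengths and limitations says of the study that "it does not include a matched active control group". Controls therefore have no sessions of any kind to miss.

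Under Statistical analysis, the main mixed models are fitted to whatever data are available. One sensitivity analysis fills missing follow-ups by last observation carried forward. The plan then adds "sensitivity analyses restricted to those participants attending at least 80 % of the sessions", which on twelve sessions means ten or more attended.

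No passage says that participants withdrawn for poor attendance are still invited to the follow-up tests, or that everyone randomised is analysed in the allocated arm.

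**The concern.** Attendance is observed after randomisation and may well track health, motivation and cognition in people aged 65 to 80. A rule that ends study participation for poor attenders, and can act in one arm only, may leave a selected EG at follow-up facing a CG not selected in that way. If poor attenders would have scored worse, the workshop looks better than it is. Losing them also removes the participants who received least of the intervention and would dilute any effect.

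These missing outcomes would be of the trial's own making, and an outcome that was never collected cannot be recovered at analysis. Carrying the last observation forward substitutes an earlier score and does not recover the missing one.

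**Working it through.** The plan gives no figure on this point, so the size can only be illustrated.

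**Inputs from Sample size calculation:** SD 4.19; target difference 2 RBMT-3 points; two-sided alpha 0.05; 90 EG and 105 CG randomised; expected losses 20% in EG and 40% in CG.

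**Assumptions, not in the documents:** 10% of EG withdrawn for non-attendance; those retained have a mean outcome 0.5 SD better than those withdrawn; no true effect; no other selective loss in either arm; baseline/follow-up correlation r of 0.5 to 0.8.

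**1. Gap not visible at baseline.** The retained EG mean exceeds the full EG mean by share withdrawn × gap:
- 0.10 × 0.5 = 0.05 SD
- 0.05 × 4.19 = 0.21 points, about 10% of the 2-point target

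**2. Type I error for that case, in a plain comparison of follow-up means.**
- Evaluable EG: 90 × 0.8 × 0.9 ≈ 65. Evaluable CG: 105 × 0.6 = 63.
- Standard error in SD units: √(1/65 + 1/63) = 0.177
- Shift: 0.05 / 0.177 = 0.283
- Rejection rate: P(Z > 1.96 − 0.283) + P(Z < −1.96 − 0.283) ≈ 0.059

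The rate depends on the model's precision. For a contrast in change, the standard error is multiplied by √(2(1 − r)). That factor is 1 at r = 0.5, which leaves the rate at 5.9%. At r = 0.8 it is 0.63, and the rate is about 7%.

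**3. Gap already present at baseline.** The withdrawn participants' baseline scores stay in the available-data model and account for a fraction r of the gap. The remaining bias is 0.10 × 0.5 × (1 − r) × 4.19:
- r = 0.5: 0.21 × 0.5 ≈ 0.10 points
- r = 0.8: 0.21 × 0.2 ≈ 0.04 points

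That is 2% to 5% of the target.

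**4. Cross-check by simulation.** With 20% of EG removed and a correlation of 0.3 between attendance and outcome, adjusting for baseline left about 0.00 SD when attendance depended only on the baseline score. It left +0.07 SD (about 0.3 points) when attendance depended on the part of the outcome not seen at baseline.

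**5. The 80% set, which is a separate analysis.** Suppose 70% of EG qualify and the gap is 0.3 or 0.5 SD. The same formula gives 0.30 × 0.3 × 4.19 = 0.38 points, or 0.30 × 0.5 × 4.19 = 0.63 points. With about 50 EG (90 × 0.8 × 0.7) against 63 CG, the rejection rates are about 8% and 12%. These figures compare follow-up scores; a constant gap would cancel from a group-by-time contrast within that set. They must not be added to the 0.21 points, because anyone who misses more than half the sessions is already outside the 80% set.

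**The case against.** The strongest reply has four parts.

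- **The rule is permissive.** It sits in a list with illness, death and loss to follow-up, like ordinary wording on reasons for discontinuation. That stands in part: the harm depends on how often the rule is used, and loss of the follow-up tests is an inference. But the text says withdrawal from the study, and nothing in it keeps these people in follow-up.
- **The planned model protects.** That holds as far as observed data explain the missingness, as steps 3 and 4 show. It does not hold for the part that baseline does not capture.
- **The direction is not established.** That stands. The documents report no link between attendance and outcome, and without one the bias is zero. The plan also expects larger losses in CG (40% against 20%), so the net attrition bias could differ in size or sign. This does not justify a further exclusion that can act in one arm only.
- **The 80% analysis is only a sensitivity analysis.** That stands. A reader might infer that both attendance rules break the main randomised comparison, or that the 8% and 12% error rates apply to it. The documents do not support this: the 80% set is run in addition to the main model and leaves its estimate unchanged. A reader might also take that set to contain no controls. That would leave nothing to compare, so the workable reading is that EG alone is restricted.

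**Conclusion.** The point holds for the withdrawal rule. As written, the rule permits discretionary missing outcomes in EG only, in the analysis that carries the main conclusion, and these could be avoided. The direction probably favours the workshop but is unproven.

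Under the assumed 10% withdrawn and 0.5 SD gap, the effect is modest: at most about 0.21 points with a type I error of about 6% if baseline does not show the gap, and about 0.04 to 0.10 points if it does. It would be larger with more withdrawals or a wider gap, and nil if attendance is unrelated to outcome. The case for changing the rule rests on its being needless and cheap to remove, more than on a large expected bias.

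The secondary point also holds. The 80% analysis compares selected attenders with unselected controls, so its agreement with the main result would not corroborate it.

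**What to change.** Remove non-adherence as a reason for withdrawal from study follow-up. State that all randomised participants are invited to both follow-ups whatever their attendance, and that they are analysed in the allocated arm. Whether someone stops attending the workshop is a separate matter and is left as it is. The cost is a change of wording and some follow-up visits for non-attenders.

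For the 80% analysis, the least change is to label it a non-randomised comparison that does not support the main result. Alternatively, replace or supplement it with a complier-average estimate that uses randomised arm as the instrument, the attendance already recorded (Intervention-related variables), and all controls. That estimate has a wider interval and needs the exclusion restriction. If number of sessions is the exposure, it also needs a dose-response assumption.

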### Secondary outcomes

*Health-Related Quality of Life* (HRQoL) will be assessed using the Short Form-36 (SF-36) [26, 27], with a validated Spanish version [28, 29]. Of the 36 items, 35 make up eight scales: physical functioning, role limitations due to physical functioning, bodily pain, general health perceptions, vitality, social functioning, role limitations due to emotional problems, and mental health [26].

*Functionality and disability* will be measured with the Spanish Version of the Short-Form Late-Life Function and Disability Instrument (SFLLFDI) [30, 31]. The LLFDI was developed as a comprehensive assessment of function and disability for use in community-dwelling older adults. It contains items that represent functional limitations (inability to perform discreet physical tasks encountered in daily routines) and disability (inability to take part in major life tasks and social roles).

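### Withdrawal criteria a) and d) can end study follow-up, not only workshop attendance, for health events that bear on the quality-of-life and disability outcomes

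*Protocol article*

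**What the plan says.** Under Study setting and participants, the protocol article states that "a participant may be withdrawn from the study if deemed necessary by the researchers based on any of the following withdrawal criteria: a) adverse experience". Criterion d) in the same list is "clinical conditions not allowing the participant to continue in the study (such as illness and accident". The list also contains non-adherence, loss to follow-up and death. In every case the withdrawal is from the study. The section does not distinguish leaving the workshop from leaving the assessments, and the article does not say that withdrawn people are still assessed.

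The secondary objective is "To assess the effect of the memory training workshop on HRQoL and on late-life function and disability". Under Secondary outcomes, quality of life "will be assessed using the Short Form-36 (SF-36", and the SFLLFDI covers "functional limitations (inability to perform discreet physical tasks encountered in daily routines) and disability (inability to take part in major life tasks and social roles". Table 1 schedules both instruments at baseline and at both post-tests.

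Under Statistical analysis, effect measures at each follow-up are computed for every outcome. The mixed models, specified for the main outcomes, use whatever scores were observed. The missing-data sensitivity analysis replaces a missing post-test with the participant's preceding score (LOCF).

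**The concern.** In people aged 65 to 80, illness and accidents are among the main things that lower SF-36 and SFLLFDI scores. If such an event can also lead to removal from the study, the reason for a missing score is tied to the value it would have had. When the event falls after the last recorded assessment, earlier scores do not predict the loss, so missing-at-random is hard to defend. LOCF is no test of this, because it fills the gap with the score from before the event.

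The loss would be partly self-inflicted. Someone who has to stop the workshop may still be able to answer questionnaires at the post-tests. Scores that are never collected cannot be recovered by any later analysis plan. At stake are the secondary comparisons and, less directly, the memory tests.

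**Working it through.** The plan gives no figure to reproduce here. The check sets the passages side by side and then illustrates the possible size.

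**Text check**

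1. Level of removal: from the study, for all listed criteria.
2. Discretion: the researchers may withdraw someone if they judge it necessary; they are not obliged to.
3. Scope: a) has no severity limit. d) is limited to conditions that prevent continuing, but continuing in the study is not split into attending sessions and being assessed.
4. Link to outcome: the events in a) and d) bear on what SF-36 and SFLLFDI measure.
5. Repair in the analysis: observed-score analysis and LOCF only.

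**Illustration, with no true treatment effect**

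All inputs are assumptions, since the documents give no event rate:
- q = share of each arm with a health event, equal in both arms: 5% to 15%
- D = drop in score caused by the event: 0.5 to 1.0 SD
- r = share of those affected who are removed before the drop is recorded

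After removal, the affected share still in an arm is q(1 − r) out of 1 − qr, so the observed mean shift is

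m(r) = −D·q·(1 − r)/(1 − q·r), against a full-cohort shift of −D·q.

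*Equal removal, r = 0.5 in both arms.* Between-arm bias is 0. Each arm's mean is still too high:
- q = 0.05, D = 0.5: 0.025 − 0.0125/0.975 = 0.025 − 0.013 = 0.012 SD
- q = 0.15, D = 1.0: 0.150 − 0.075/0.925 = 0.150 − 0.081 = 0.069 SD

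*Unequal removal, 80% in one arm and 40% in the other.* The bias favours the arm with more removals:
- q = 0.05, D = 0.5: 0.015/0.98 − 0.005/0.96 = 0.0153 − 0.0052 = 0.010 SD
- q = 0.15, D = 1.0: 0.090/0.94 − 0.030/0.88 = 0.0957 − 0.0341 = 0.062 SD

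*Extreme, 100% against 0%.* The bias is D·q, from 0.025 to 0.15 SD.

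*LOCF in the 80%/40% case.* Removed people are given their pre-event score, so an arm's shift is −D·q·(1 − r) and the bias is D·q·(0.8 − 0.4): 0.010 SD (q = 0.05, D = 0.5) to 0.060 SD (q = 0.15, D = 1.0). This is almost the same as without imputation, so agreement between the two analyses would not reassure.

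**Scale.** With the 75 per group named in the Sample size calculation, the standard error of a difference in means is √(2/75) = 0.163 SD. The 0.062 SD figure is 0.062/0.163 = 0.38 standard errors.

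**The case against.** The strongest reply is that the rule is narrower than it first appears. Withdrawal is optional, and d) applies only where the condition prevents continuing. Assessments are in-person interviews at the health care center, about 90 minutes at follow-up, so some people who meet d) could not be assessed under any rule. The list also includes death and loss to follow-up, which nobody chooses, so part of it reads as a catalogue of reasons for discontinuation. The article is condensed, and handling of withdrawn participants may be described in a fuller document. The affected outcomes are secondary.

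Most of this stands and limits the point. A reader might infer that participants whose health worsens will leave the study. The text says only that they may be withdrawn.

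A reader might also infer that events are noticed sooner, and removal is likelier, in the experimental group (EG) because "The intervention will consist of twelve 90-minute group sessions provided once a week by a psychologist specialized in memory training", while the control group (CG) attends only the assessments. The documents do not support that:
- They do not describe how illness or accidents become known in either arm.
- Weekly contact covers only the session period.
- All participants are registered at the participating centers, so events in CG could surface there.
- The only arm-specific losses stated run the other way, 20% in EG and 40% in CG. They are not split by reason, so they settle nothing about illness.
- The one criterion that is arm-specific by construction is "significant non-adherence to the intervention (missing more than 50 % of the sessions", which is a separate matter.

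The reply does not remove two things. Criterion a) has no severity limit, and the stated level of withdrawal is the study. That is a rule written in the article, not a detail it leaves out.

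**Conclusion.** The point holds in a limited form. The withdrawal rule permits discretionary removal from follow-up for health events related to SF-36 and SFLLFDI, and the planned analyses do not address the informative loss that could follow.

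The direction of any between-arm bias cannot be read from the documents. Its size is zero with equal removal and about 0.01 to 0.06 SD under the 80% versus 40% assumption, which is small against the trial's precision. It reaches 0.15 SD only in the most extreme case considered. Each arm's own mean is flattered whenever affected people are removed, by 0.01 to 0.07 SD at 50% removal. These figures rest on assumed event rates, score drops and removal shares, and on the drop not having been recorded before removal. A claim that the trial is biased in favour of EG would go beyond the text. This is a worthwhile, inexpensive improvement, not a flaw that undermines the trial.

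**What to change.** Reword criteria a) and d) so that they end workshop attendance only. End study follow-up only for withdrawal of consent, death or inability to be assessed. Invite all other randomised participants, in both arms, to the immediate and delayed post-tests, analyse them in the group to which they were randomised, and record the reason and date of stopping.

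Optionally, where an in-person visit is impossible, collect the self-report measures (SF-36, SFLLFDI, MFE and the 0-10 memory score) by telephone or post.

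The cost is a change of wording and a few more visits or calls by the existing data collectors. If the option is used, some questionnaires will have been completed in a different mode, which should be recorded. The clinical decision whether someone stops the workshop is unchanged.
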